## Abstract

**Background:**

The superiority of tenotomy vs. tenodesis for surgery on lesions of the long head of the biceps brachii tendon is still under debate. Indeed, high-quality evidence is lacking, mainly because of methodological problems, such as retrospective design, population sample size or lack of patient randomization.

**Methods/Design:**

The study will be a two-center, double-blind, randomized, controlled trial to compare patients treated with biceps tenotomy or tenodesis for lesions of the long head of the biceps brachii tendon over a 2-year follow-up period. The study participants will be 128 adults with biceps brachii tendinopathy and supraspinatus tendon tears. The primary end point will be the postoperative difference in the Constant-Murley score (CMS) between the 2 groups at the two-year follow-up. A comparison of the mean improvement with standard age- and gender-related CMS will be performed. The secondary end point will be evaluation of the postoperative general health of patients, as evaluated with Short Form 36 (SF-36) scores. The number and severity of complications associated with use of the different surgical techniques will be assessed.

**Discussion:**

This study will be the first randomized and appropriately powered clinical trial to directly compare tenotomy and biceps tenodesis. The results of this study will help to establish clinical practice guidelines for patients suffering from lesions of the long head of the biceps brachii tendon, providing important information to patients and health care providers about the possible complications, outcome predictors and effectiveness of the targeted interventions.

**Trial Registration:**

Current Controlled Trials ISRCTN38839558

## Background

Lesions of the long head of the biceps brachii tendon (LHBT) are common
[1,2], and when not adequately treated, they may be responsible for persistent pain, as well as functional impairment of the shoulder
[3]. LHBT lesions can be isolated
[4] but are more frequently associated with more complex disorders, such as shoulder instability or supraspinatus tendon tears
[5-7]. The decision about whether to proceed with conservative
[8-12] or surgical management of LHBT lesions might depend on the associated shoulder disorders and the duration of the symptoms
[13].

The two most common procedures for LHBT lesions are biceps tenotomy and biceps tenodesis
[14]. Currently, there is no consensus regarding the most effective surgical procedure because of the inconsistent results and the limitations of the published studies
[15,16]. Some authors have claimed that tenotomy is superior and reported satisfactory results in most patients treated with this technique
[17-19]. Tenotomy has the advantages of easier execution and, when performed alone, the requirement of fewer restrictions during the postoperative period with an earlier return to activity
[15]. Other authors reported similarly good results in most patients treated with tenodesis of the LHB
[20-23]. This technique seems to be able to prevent some of the most common complications associated with tenotomy, such as cramping of the brachial biceps muscle and retraction of the biceps tendon
[18,24]. The latter complication, referred to as Popeye’s sign or Popeye’s deformity, occurs in 3-70% of patients undergoing tenotomy of the LHBT and results in a cosmetic deformity
[17,20]. Further possible complications related to the intervention represented by tenotomy include decreases in the strength of flexion and supination of the arm and forearm, respectively
[11,25]. However, these findings are not consistent with the results reported by others
[16,24,26].

Most of the studies that compare the results of LHB tenodesis and tenotomy are limited by methodological deficiencies, such as retrospective design, low statistical power or lack of patient randomization
[14]. To the best of our knowledge, there are no double-blind randomized controlled trials on this topic. The purpose of this double-blind randomized trial is to compare the effectiveness of tenodesis and tenotomy in the treatment of LHBT lesions.

## Methods/Design

This will be a two-center, double-blind, randomized, prospective study of all consecutive patients to be treated for LHBT lesions with biceps tenotomy or biceps tenodesis, including a 2-year follow-up period.

This study will require 12 months for patient enrollment and an additional 2 years for the completion of follow-up over a total of 3 years.

### Aims and hypothesis

This study will seek to compare the efficacy of biceps tenotomy and biceps tenodesis in the treatment of LHBT lesions. The primary end point will be the postoperative differences in Constant-Murley scores (CMS) between the 2 groups at the two-year follow-up. The secondary end point will be evaluation of the general health of patients in both groups as evaluated by Short Form 36 (SF-36) scores. The number and severity of complications associated with the investigational surgical techniques will be assessed. The null hypothesis is that there will be no difference in the mean CMS between the tenotomy and tenodesis groups.

### Inclusion and exclusion criteria

A screening interview will be conducted to ensure that the referred patients meet the inclusion/exclusion criteria prior to performing study-specific tests. A thorough physical examination and an MRI of the shoulder will be performed for identification and characterization of the pathology. The diagnosis will be verified by arthroscopy.

Male or female patients, aged 40 years or older, with LHBT lesions (tenosynovitis, subluxation, dislocation or partial rupture of the tendon) associated with grade I or II full-thickness supraspinatus tendon tears
[27] will meet the criteria for enrollment. If any of the following criteria apply, patients will be excluded: (1) previous surgery of the affected shoulder, (2) insufficient comprehension of the Italian language to understand the trial features, (3) mental handicap, (4) a lack of willingness to return for all scheduled follow-up visits, (5) participation in another study, (6) any previous upper extremity neurological disorder or diagnosis based upon physical examination, (7) complaint of pain in both shoulders, (8) a life expectancy of less than 2 years, (9) an ongoing insurance trial, lawsuit, or pending legal action for shoulder disease.

Patients who do not meet all of the inclusion criteria and patients who meet any of the exclusion criteria will automatically be excluded from the study. Informed consent will be obtained from each patient.

### The number and source of patients

Patients will be recruited from the outpatient clinic. The goal is to assess 128 participants for the study. We performed a priori power analysis to determine the sample size required to achieve the pre-specified power level (1 - β), significance level α, and the population effect size for the CMS between the two treatment groups to be assessed. In a previous study, the CMS was normally distributed within some subject groups
[28]; therefore, we will use an unpaired t-test with an associated medium effect size equal to 0.5. Under these conditions, we will need to study 64 subjects for each group to be able to reject the null hypothesis that the population means of the groups are equal with a probability (power) of 0.8 and that the Type I error probability is equal to 0.05. Considering the same significance and power level, this sample size will allow us to detect an effect size that is equal to 0.35 for the null hypothesis that the population means of CMS scores before and after treatment are equal. Because of the possibility that participants could drop out of the protocol, a total of 150 patients will be recruited for the trial. G*Power software (Institut fur Experimentelle Psychologie, Heinrich Heine Universitat, Dusseldorf, Germany) was used for the power analyses.

### Randomization

After the participants have gone through the screening process and are determined to meet the enrollment criteria, they will be randomized to the treatment groups (i.e., biceps tenotomy or biceps tenodesis). The patients will be randomly allocated to the groups using specific software (Filemaker Pro 12, Santa Clara, CA, USA) with an allocation ratio of 1:1; they will be unaware of which surgical treatment they will receive. Patients will be fully informed that they have a 50% chance of receiving LHB tenotomy and that there will be no opportunity for cross-over treatments.

An independent secretary will organize treatment allocation by distributing sealed numbered envelopes to the nurse manager in the operation theatre. A nurse will open the envelope only when a preoperative diagnostic evaluation has documented the LHBT lesion and supraspinatus tendon tear.

### Imaging

Preoperative radiological examination will include anterior-posterior (AP) and outlet X-ray and a 1.5-T non-arthrographic MRI of the shoulder (Magnetom® Symphony-Maestro-Class, Siemens AG, Erlangen, Germany). Indeed, non-contrast MRI has been reported to be 98% sensitive and 89.5% specific for biceps tendon pathology
[29]. Imaging scans will include a fast spin-echo intermediate-weighted axial sequence, a fast spin-echo coronal oblique intermediate-weighted sequence, and coronal oblique and sagittal oblique fast spin-echo T2-weighted acquisitions with fat suppression. A full-thickness tear will be defined as a high T2 signal extending through the depth of the supraspinatus tendon
[30].

Reports will be generated by two musculoskeletal radiologists who will be blinded to the clinical characteristics of the patients, and their evaluation will be repeated on two separate days. Cohen’s kappa coefficient for the inter-observer and intra-observer reliability of scoring will be calculated. A consensus decision on the presence of supraspinatus tendon tear and LHBT lesion (i.e., tenosynovitis, subluxation, dislocation or partial rupture) will be reached in a final common readout.

### Biceps Tenotomy

Tenotomies will be performed through the anterior glenohumeral portal. A blunt probe will be used to pull the extra-articular portion of the biceps into the glenohumeral joint to allow for visual inspection of the macroscopic structural changes
[31]. The biceps tendon will then be released from its insertion on the superior glenoid labrum using arthroscopic electrocautery.

### Biceps Tenodesis

A biceptor^TM^ tenodesis system (Smith & Nephew Inc, Memphis, TN, USA) will be used during the procedure. A spinal needle will be inserted at the anterior-lateral edge of the acromion into the shoulder joint and through the biceps. A monofilament suture will be introduced through the needle and the biceps tendon. Then, the long head of the biceps tendon will be cut at its insertion point through the rotator interval portal under the glenoid labrum. Both arms of the suture will exit the anterior portal. The biceps tendon will be mobilized out of the bicipital groove, and the desired position for reattaching the tendon will be located. A 2.4-mm guide wire will be drilled perpendicularly to the humeral shaft in the bicipital groove. A reamer appropriate to the screw diameter will be used to drill a 25-30-mm deep hole for definitive tendon attachment.

A tendon fork will be placed after tension release of the tendon, and the tendon will be inserted into the prepared hole up to the far cortex. The tendon will subsequently be pinned in place and a biosure peek-optima® (Smith & Nephew Inc, Memphis, TN, USA) interference screw will be inserted over this pin. The excess tendon will be trimmed.

### Postoperative rehabilitation

The operated shoulder will be immobilized for 3 weeks using a sling with an abduction pillow. Pendulum exercises will be allowed, starting from the first postoperative day. After the immobilization period, passive and assisted exercises in forward flexion and external rotation will be initiated. Strengthening exercises will be restricted until 6 weeks after the surgical procedure. Three months after the operation, patients will be allowed to engage in light sports activity. Heavy manual work and overhead motion will be allowed after 6 months.

[44] strength measurements. External shoulder rotation will be tested with the shoulder in a neutral position and the elbow in 90° of flexion. The strap of the myometer will be applied to the distal forearm of the patient. When measuring shoulder strength during external rotation with the arm at the side, the subject will be asked to externally rotate only the forearm with the elbow kept at the side to prevent compensation from motion of the torso or extension-abduction of the humerus. Abduction shoulder strength will be tested with the patient in the standing position and the arm in 90° of abduction in the scapular plane with the elbow extended and the forearm pronated, and resistance will be applied to the wrist. If 90° of abduction cannot be achieved, abduction strength will automatically be considered zero. To prevent leaning toward the contralateral side and the additional use of the trunk muscles, stabilization of the torso will be achieved by direct contact of the contralateral shoulder and trunk with a wall. Scapular rotation will be restricted by the examiner’s hand. Forearm supination will be tested with the elbow in 90° flexion, maximal pronation and 0° pronation/supination. Stabilization straps will be secured and foot markers noted during all testing to ensure a standardized and reproducible protocol. Three submaximal effort trials will be performed in each axis to acquaint the patient with the testing conditions. Three maximal effort trials will be performed in each axis and the recorded values will be averaged to measure the strengths. A 5-minute rest period will be allowed between each testing period.

The normal contralateral upper extremity will be used as a matched control in the evaluation of the postoperative biceps strength measurement without adjusting the results for handedness because no significant differences have been observed between the dominant and nondominant side of healthy volunteers
[25]. Thus, the achieved average elbow flexion strength of the affected arm will be compared with the healthy opposite side of the patient, and the percentage will be graded between 0 and 20 points, as previously described
[45]. In this regard, 20 points will be given to a performance of 91% and above; 16 points, between 90% and 81%; 12 points, between 80% and 71%; 8 points, between 70% and 61%; 4 points, between 60% and 51%; and 0 points to a performance below 50%.

The SF-36 is a validated, multi-purpose, short-form health survey with 36 questions, which combine eight health domains into a physical (PCS) and mental component scale (MCS)
[46]. The PCS combines the health domains of physical functioning (PF), role limitations due to physical health (RP), bodily pain (BP), and general health perceptions (GH). The MCS combines the health domains of vitality, energy, or fatigue (VT), social functioning (SF), role limitations due to emotional problems (RE), and general mental health (MH). SF-36 scores range from zero to 100 points with lower scores indicating poorer function
[47,48]. The postoperative difference in the SF-36 scores between the 2 groups will be evaluated at the two-year follow-up.

At the final follow-up, the patients and the blinded investigator will be asked to guess which treatment they believe the patient received to assess blinding and randomization.

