## Discussion

To the best of our knowledge, this will be the first double-blind randomized controlled trial to compare clinical scores of tenodesis and tenotomy in the treatment of LHBT lesions. There are a few studies in the literature that directly compare the results of these techniques, and most of them reveal no differences between treatments
[11,24-26,49,50]. Boileau *et al.* retrospectively evaluated 68 patients with irreparable rotator cuff tears treated with isolated arthroscopic biceps tenotomy or tenodesis and reported similar outcomes after both procedures
[24]. Osbahr *et al.* retrospectively studied 160 patients with chronic refractive bicipital pain, treating half of the patients with tenotomy and the other half with tenodesis
[49]. They found no significant difference between the two treatment methods in terms of cosmetic deformity, muscle spasm or anterior shoulder pain. Similarly, when twenty patients who underwent biceps tenotomy or tenodesis for chronic tenosynovitis were compared retrospectively, no difference in the functional or cosmetic results was observed
[50].

Wittstein *et al.* showed no significant difference in postoperative scores between the two techniques in a cohort study of 35 patients
[25]. The major limitations of this study were a lack of randomization of participants receiving tenotomy or tenodesis and a limited number of participants. In agreement with a retrospective study
[11], the authors also found that tenotomy decreased forearm supination compared with tenodesis. These findings were not confirmed in other studies, which reported no difference between these techniques
[16,24,26]. Shank *et al.* compared the forearm supination and elbow flexion strength of the upper extremity and found no significant difference between the tenotomy, tenodesis, and control groups
[26]. However, they did not report the clinical scores after these surgeries
[26]. Koh and colleagues demonstrated that neither clinical scores nor total surgical times revealed significant differences between tenotomy and tenodesis
[16]. Notably, this study was not a randomized trial, and the study group was underpowered for most of the outcomes. Therefore, the authors acknowledge that their results should be interpreted with care.

The need for appropriately powered, well-conducted, randomized, controlled trials that compare the outcomes of these procedures has recently been emphasized

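### The 0–20 elbow-flexion score leaves 50% unscored and, with its ceiling at 91% and ten-point bands, is a weaker basis for comparing the arms than the strength ratio itself (minor)

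*Protocol article*

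**What the plan says.** All of this stands in the protocol article under Baseline and follow-up measurements, unless noted.

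- **Measurement.** "Three maximal effort trials will be performed in each axis and the recorded values will be averaged to measure the strengths". For elbow flexion, "the achieved average elbow flexion strength of the affected arm will be compared with the healthy opposite side of the patient".
- **Scoring.** The resulting percentage is graded, with a reference to an earlier report [45]: "20 points will be given to a performance of 91% and above; 16 points, between 90% and 81" per cent; "12 points, between 80% and 71%; 8 points, between 70% and 61" per cent; "4 points, between 60% and 51%; and 0 points to a performance below 50" per cent. No rounding rule is given.
- **Handedness.** The opposite arm serves as control "without adjusting the results for handedness because no significant differences have been observed between the dominant and nondominant side of healthy volunteers", citing reference [25]. Dominant arm and surgical side are both recorded.
- **Status.** Aims and hypothesis names the CMS as primary end point and the SF-36 as secondary. The sample size rests on the CMS. Statistical analysis neither names the 0–20 score nor assigns it a test.

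**The concern.** A scoring rule should give every possible value one score. This one does not. The percentage is one average divided by another, so it is continuous, while the bands are written as though only whole numbers occur. Even in whole numbers, 50 belongs nowhere.

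The second problem remains after the gaps are closed. A patient at 91% and one at 110% score the same, as do patients at 81% and 90%. If most patients recover well, a large share sits at the maximum and the score can hardly separate the arms. The Background lists reduced flexion strength among the possible complications of tenotomy and says that reports conflict. A blunt score makes another inconclusive result on that question more likely.

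**Working it through.** **1. The plan's own figure.** The article states 64 per group for an effect size of 0.5, power 0.8 and alpha 0.05, for the CMS. For a two-sided unpaired t-test the noncentrality is 0.5 × √(64/2) = 2.83 on 126 degrees of freedom. Power is 0.801 at 64 per group and 0.795 at 63, so the stated figure reproduces. No power is stated for the flexion score. Below, 64 per arm and 0.5 SD are borrowed from the CMS calculation for illustration.

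**2. The bands.**

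| Points | Percentage as printed | Open interval just below |
|---|---|---|
| 20 | 91 and above | 90–91 |
| 16 | 81–90 | 80–81 |
| 12 | 71–80 | 70–71 |
| 8 | 61–70 | 60–61 |
| 4 | 51–60 | 50–51, including 50 itself |
| 0 | below 50 | none |

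Under any reading, exactly 50 has no score. Without a rounding rule the five intervals are open, and the score depends on who computes it: 90.6% earns 20 points if rounded to the nearest percent and 16 if truncated.

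**3. Share of patients in a gap.** The article gives no mean or SD for the ratio. I assume a normal distribution with mean μ of 80–100% and SD σ of 10–20 points.

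- *Unrounded.* The share is the sum over the five intervals of Φ((b − μ)/σ) − Φ((a − μ)/σ). For μ = 90, σ = 15: 0.0008 + 0.0038 + 0.0114 + 0.0218 + 0.0266 = 0.064, and 0.064 × 128 = 8.2 patients. The extremes are 0.095 (12.1 patients; μ = 80, σ = 10) and 0.032 (4.1 patients; μ = 100, σ = 10). The range is about 3–10%.
- *Rounded to whole percents.* Only 50 stays open, with share Φ((50.5 − μ)/σ) − Φ((49.5 − μ)/σ). The largest value is 0.0065 (μ = 80, σ = 20), and 0.0065 × 128 = 0.83 patients.

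**4. Share at the maximum.** With rounding this is 1 − Φ((90.5 − μ)/σ): 0.15–0.30 at μ = 80, 0.29–0.39 at 85, 0.48–0.49 at 90, 0.59–0.67 at 95 and 0.68–0.83 at 100.

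**5. Power on the ratio and on the score.** Simulation with 64 per arm, means differing by 0.5 SD, t-tests at 0.05 and 20,000 runs per cell. Values were rounded to whole percents and 50 was scored 0, so the loss shown comes from the banding and the ceiling, not from the gaps.

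| Mean of better arm | Ratio | Score, SD 10 | Score, SD 15 | Score, SD 20 |
|---|---|---|---|---|
| 80% | 0.80–0.81 | 0.76 | 0.77 | 0.77 |
| 85% | 0.80–0.81 | 0.75 | 0.77 | 0.75 |
| 90% | 0.80–0.81 | 0.73 | 0.73 | 0.73 |
| 95% | 0.80 | 0.66 | 0.69 | 0.70 |
| 100% | 0.80 | 0.56 | 0.63 | 0.66 |

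The simulation error is about √(0.75 × 0.25/20,000) = 0.003. A repeat with 100,000 runs per cell agreed to within 0.01.

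**The case against.** **The gaps are mostly a matter of reading.** Whole-percent bands imply whole-percent values, and then only 50 is open. This stands. A reader might infer that 3–10% of patients cannot be scored, but that follows only if nobody rounds. The article does not say so and its bands suggest the opposite.

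**The scale is borrowed.** It is attributed to reference [45], which may settle the boundary and the rounding. That cannot be checked here. Still, the article prints the rule in full, and as printed it omits 50.

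**No powered comparison is harmed.** This also stands. The score is neither the primary nor the secondary end point, and it is not among the four CMS subscales that the article lists. The power figures rest on assumed means and SDs and on an effect size that the article sets only for the CMS. Nor does the article say that the score replaces the raw values; Statistical analysis provides t-tests for continuous measures. It does not say, however, which of the two will be used to compare the arms.

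**Handedness.** A reader might infer that the article contradicts itself, because it relies on reference [25] here while its Discussion says of that study: "The major limitations of this study were a lack of randomization of participants receiving tenotomy or tenodesis and a limited number of participants". The documents do not support this. The criticism concerns the comparison of the two operations "in a cohort study of 35 patients", whereas the handedness statement concerns healthy volunteers, whose number is not given. A non-significant difference does not prove equality, but the strength of that evidence cannot be judged from the article. With 1:1 randomization, operated-arm dominance is balanced in expectation, so leaving it out adds noise and does not bias the comparison of arms.

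**Conclusion.** The point holds as a minor one. Certain from the text alone: exactly 50% has no score, no rounding rule is stated, and every value of 91% or more scores the maximum. With rounding, the gap is expected to affect fewer than 1 of 128 patients.

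The ceiling and the coarse bands matter more. Against about 0.80 on the ratio, the assumed scenarios cost roughly 3 to 5 points of power when the better arm averages 80–85%, 7 to 8 at 90%, 10 to 14 at 95% and 14 to 25 at 100%. These sizes assume normal ratios, SDs of 10–20 points, a 0.5 SD difference and a t-test on the score. None of these is given for this measure. The direction of the loss is the same in every scenario, and its size grows with how well patients recover.

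It would be wrong to infer that the trial loses power for its main question. The CMS calculation still gives 0.801 at 64 per group, and the SF-36 is untouched.

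**What to change.** Compare the arms on the continuous operated/contralateral flexion ratio at 24 months, adjusted for its baseline value and for whether the operated arm is the dominant one. Dominant arm and surgical side are already recorded; adjusting for dominance mainly reduces noise. The article plans baseline strength testing but mentions the opposite arm only for the postoperative comparison, so confirm that both arms are tested at baseline.

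Keep the 0–20 score as a description only. Make its bands contiguous, for example above 90, above 80 to 90, above 70 to 80, above 60 to 70, above 50 to 60, and 50 or below. State the rounding rule before any data are seen.

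The sample size does not change, and if both arms are already tested at baseline the change is one of wording. The cost is a less direct comparison with earlier reports that used the banded score; reporting it descriptively keeps most of that link.
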